### Adjuvant and neoadjuvant therapy

In accordance with the Chinese Colorectal Cancer Diagnosis and Treatment Standards 2020 and NCCN (2022 V2), the internal medicine treatment plan of this study was formulated [5, 8].

#### Neoadjuvant therapy

Neoadjuvant chemoradiotherapy is recommended for rectal cancer <12 cm from the anus. Neoadjuvant chemoradiotherapy: Long-course chemoradiotherapy is used and a total dose of 45.0–50.4 Gy is recommended for primary tumors and high-risk areas, with 1.8–2.0 Gy each time, for a total of 25–28 cycles. During radiotherapy, 5-FU or capecitabine monotherapy is given concurrently. The specific situation of neoadjuvant therapy is as follows: (i) Direct surgery is recommended for patients with Tl–2N0M0 or for those with contraindications to radiotherapy and chemotherapy, and neoadjuvant therapy is not recommended. (ii) For patients with resectable rectal cancer with T3 and/or N^+^, preoperative neoadjuvant chemoradiotherapy is recommended in principle; neoadjuvant chemotherapy alone can also be considered after multidisciplinary treatment discussion and then combined with radiotherapy on the basis of efficacy evaluation, with preoperative chemoradiotherapy recommended for patients with stage T4 disease. (iii) For patients who are not suitable for radiotherapy, it is recommended to decide whether to undergo simple neoadjuvant chemotherapy based on multidisciplinary treatment discussions (refer to the Chinese Colorectal Cancer Diagnosis and Treatment Standards 2020).

#### Adjuvant therapy

Adjuvant therapy should be determined on the basis of the patient’s primary site, pathological stage, molecular indices, and postoperative recovery. Adjuvant chemotherapy should be started ∼4 weeks after surgery (appropriately extended for those with poor physical fitness) and the chemotherapy time limit is 3–6 months. During treatment, the dose of the drug should be adjusted and/or the duration of chemotherapy should be shortened according to the patient’s physical condition, drug toxicity, postoperative TN stage, and patient preference. Adjuvant therapy is not recommended for patients with contraindications to chemoradiotherapy:

I: Adjuvant therapy is not recommended for stage I (T1–2N0M0) rectal cancer.II: (i) Adjuvant chemotherapy is recommended for stage II rectal cancer with the following high-risk features: poor histological differentiation (DI or IV) with normal mismatch repair (pMMR) or microsatellite stabilization (MSS), T4, vascular lymphatic invasion, preoperative intestinal obstruction/intestinal perforation, insufficient lymph nodes detected in the specimen (<12), nerve invasion, and positive resection margins. The chemotherapy regimen is CapeOx, FOLFOX, or single-agent therapy such as 5-FU/LV, capecitabine, administered for 3–6 months. There are no risk factors and adjuvant chemotherapy is not recommended. (ii) Postoperative adjuvant chemotherapy is not recommended if the tumor tissue shows mismatch repair deficiency (dMMR) or high-level microsatellite instability (MSI-H).III: Adjuvant chemotherapy is recommended for stage III rectal cancer, and CapeOx, FOLFOX, or single-agent capecitabine, 5-FU/LV is recommended for chemotherapy. For low-risk patients (T1–3N1), 3 months of adjuvant chemotherapy with the CapeOx regimen may also be considered.IV: For T3–4 or N1–2 rectal cancer located <12 cm from the anal verge, preoperative neoadjuvant chemoradiotherapy is recommended; if there is no neoadjuvant radiotherapy before surgery, whether to undergo adjuvant chemoradiotherapy is decided on the basis of the postoperative pathological situation, among which chemotherapy is recommended to be based on fluorouracil drugs. (i) Patients with stage II–III rectal cancer who have one of the following risk factors after surgery are recommended to undergo concurrent chemoradiotherapy: circumferential resection margin (CRM) of ≤l mm, pT4b, pN2 and poor TME quality/mesorectal defect, pathology II/stage III but unable to evaluate the quality of TME surgery, nerve invasion close to MRF, pathology stage II/III but unable to assess CRM status. (2) Patients with stage II–III rectal cancer after surgery are recommended to receive concurrent chemoradiotherapy if they meet both of the following conditions: CRM of 1–2 mm and circumferential obstructive tumors. (iii) Postoperative concurrent chemoradiotherapy is not recommended for patients with stage II–III rectal cancer who meet all of the following conditions: good TME quality/smooth and intact mesorectum, pT1–3 or pT4a above peritoneal retroflexion, pN0–l, and CRM of >2 mm.

### Subject management

#### Subject exclusion criteria

After being selected for randomization, the patient requested to withdraw from the study because of various considerations.There are no data after entering the queue.Intraoperative findings of tumor involvement requiring multivisceral resection, distant metastasis, or inability to complete the planned laparoscopic radical resection.Other reasons need to be excluded as determined by the investigator.

#### Criteria and management of subject dropout

##### Shedding criteria

Any randomized participant who discontinues study participation or is lost to follow-up before completing the protocol-specified observation period will be considered a dropout.

##### Dropout treatment

When subjects drop out, the investigator will contact the subjects as much as possible by visiting their homes, making appointments for follow-up, telephone, and letters, among others, asking for reasons and to complete the evaluation items that can be completed. If the experimental case is withdrawn because of adverse reactions, the investigator should take corresponding treatment measures according to the actual situation of the subject. The relevant test data of the expulsion cases are properly maintained, i.e. they are kept as documents, and they are also required for the full analysis set (FAS) statistics. Patients who have dropped out do not need to be replaced.

### Data management

#### Data entry

Data-management personnel: Research assistants and follow-up personnel of each subcenter. Data managers should upload and review research data in a timely manner to ensure data accuracy and their main responsibilities are as follows:

Recording: synchronous data entry is performed.Auditing of data: each item in the database is checked and found to be inconsistent, and the original data are checked and corrected sequentially.During the trial, the informed consent of the subjects and the screening of inclusion should be checked regularly.Confirm that all case report forms are completed correctly and are consistent with the original data.Based on the internet database, real-time monitoring and online quality control are conducted. Once data problems are identified, telephone inquiries are conducted in time to modify the data.Withdrawals and loss to follow-up of verified participants are described in the case report form.It is confirmed that all adverse events have been documented and that serious adverse events have been reported and documented.

Statistician: [name]. Statisticians are responsible for data collection, collation, and analysis. The details are as follows:

Locking of the database: after the research is completed, the database will be locked and the locked data are not allowed to change in principle; if changes are required due to special circumstances, the data manager must apply in writing to the person in charge of the study to explain the reason for the application for unlocking, and the person in charge of the study and the statistician shall negotiate to determine whether to agree to the unlocking.Data analysis: the database is analysed according to a statistical plan.

### Data retention and summary

#### Data retention

All study data will be retained by the investigators for a minimum of 5 years after trial completion, in accordance with GCP and institutional policies.

#### Summary of the trial

After completion of the trial, all case report forms will be filled out, reviewed, and signed by the research assistant and follow-up staff according to the data-management requirements of this program and submitted to the designated person in charge of each center for preservation together with the “informed consent form.”

### Statistical methods

#### Evaluation and analysis of efficacy

FAS population: This dataset is derived from the minimal and reasonable culling of subjects from all randomized subjects, as close as possible to the population of subjects that conform to the principles of the intention-to-treat (ITT) analysis. ITT: A patient is considered an ineligible study subject and is placed in the ITT population as a result of a change in the assigned surgical regimen or the implementation of an unplanned alternative treatment on the basis of the judgment of the study group or the patient’s special condition. ITT analysis of the primary and secondary endpoints will be performed by using whole-population data.

Eligible for the protocol (PP) population: Subjects in the FAS who meet the following conditions—the baseline value of the main indicators is complete, meets the inclusion criteria and does not meet the exclusion criteria, completes the specified treatment regimen after random assignment according to the clinical trial protocol, and has good compliance. For auxiliary purposes, if the difference between the ITT and PP analysis groups is >10%, then the ITT analysis is used.

#### Safety evaluation and analysis

Safety analysis (SS) population: All subjects who have had at least one safety assessment after randomization should be included. The security analysis should use the security dataset of the analysis population. Safety datasets: Ineffective cases are considered to be the worst-case scenario, such as the evaluation of liver function, which is considered to be the worst, unlike the ITT analysis, which presents the most recent results and may be improved.

It is based mainly on the occurrence of adverse events and serious adverse events, and the population data are analysed with safety analysis.

#### Estimation of missing values for major indicators

When there are missing values in the efficacy and safety evaluation variables, the filling method is appropriately selected according to the missing rate of the main indicators. For missing data in the primary and secondary endpoints, if the missing-data rate is low (<10%), complete-case analysis will be used. If the degree of missing data exceeds 10%, then multiple imputation methods are employed. Sensitivity analyses will be performed to assess the robustness of the results to missing-data assumptions and a sensitivity analysis of the missing mechanism of the main indicators will be conducted.

#### Statistical analysis

Statistical analyses will be performed by using SPSS and systematically categorized according to the study indicators, including baseline characteristics, primary endpoint, and secondary endpoints. An interim analysis upon the enrollment of half of the anticipated sample size will be taken into consideration based on the actual progress of the participant recruitment, clinical implementation status, and data availability. Descriptive analyses of continuous data include the mean, standard deviation, median, interquartile range, and maximum and minimum values. Descriptive analysis will be used for the inclusion rate and composition ratio of the counted data. If the continuous data conform to normality and variance homogeneity, a *t*-test will be used for the comparison of significant differences and the Wilcoxon rank-sum test will be used for nonconformity. The chi-square test will be used for significant differences in count data and the Wilcoxon rank-sum test will be used for significant differences in grade data. Multivariate analysis is performed by using a logistic regression model. Kaplan–Meier analysis is used for DFS, the log-rank test is used for variability, and a Cox regression model is used for regression analysis. *P *< 0.05 will be considered to indicate statistical significance.

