### Number of research cases

This is a superiority trial. The 3-year disease-free survival (DFS) rates of patients with high inferior mesenteric artery (IMA) ligation were 86.1% and 84.5%, and the 3-year DFS rates of the experimental group (IMV high ligation and left colonic artery D3 lymph node preservation group) in this study were estimated to be 85% [12, 13]. The 3-year DFS rates of patients with low IMA ligation and 253 lymphadenectomy were 72.4% and 83.9%, respectively, and the 3-year DFS rate of the control group (IMV low ligation and left colonic artery D3 node dissection group) was estimated to be 78% [12, 13]. Assuming 3-year DFS rates of 85% (high ligation) and 78% (low ligation), a superiority margin (hazard ratio) of 0.90, *α* = 0.05, *β* = 0.8, and a superiority cutoff value of the risk ratio of 0.90, the calculation was performed by using a two-sided *α* (0.05), and the enrollment time was 2 years according to the ratio of 1:1 between the two groups, assuming that the unit enrollment rate was equal when patients were recruited and that the follow-up time was 3 years. PASS 15.0 software was used for calculations and the loss-to-follow-up rate of both groups was set at 20%; thus, 758 cases are required for each group. The total required sample size is 1,516.

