#### Randomly encoded files

Randomization form: At the end of randomization, the randomization form is exported from the IWRS, submitted to the sponsor, and sealed. Upon study database lock and sponsor approval, a randomization list is generated and provided to the project statistician.

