### Research ethics

All the participating sites are required to pass the review by the ethics committee of the center and obtain a certificate before they can conduct research. Patients or authorized family members of patients are required to sign informed consent forms prior to patient randomization. An independent Data and Safety Monitoring Board (DSMB) will be established to periodically review the accumulated safety and efficacy data. The trial may be terminated early on the basis of DSMB recommendations for compelling evidence of superiority, futility, or safety concerns.

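### The only named interim analysis is tied to half enrolment, when about 8% of the expected DFS events exist, although the DSMB may stop for superiority or futility

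*Protocol article*

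**What the plan says.** Four statements in the protocol article bear on this.

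- **Statistical analysis**, on timing: "An interim analysis upon the enrollment of half of the anticipated sample size will be taken into consideration". Whether it happens depends on recruitment progress, clinical implementation and data availability. No event count is given. The same section compares DFS by Kaplan–Meier, log-rank and Cox regression.
- **Research ethics**, on stopping: an independent DSMB is to review safety and efficacy data periodically, and "The trial may be terminated early on the basis of DSMB recommendations for compelling evidence of superiority, futility, or safety concerns".
- **Statistical analysis**, on the threshold: P<0.05 "will be considered to indicate statistical significance". This closes a general paragraph covering all the tests and is the only significance criterion given.
- **Number of research cases**, on the design: "Assuming 3-year DFS rates of 85% (high ligation) and 78% (low ligation), a superiority margin (hazard ratio) of 0.90". Patients enter at a constant rate over 2 years, are allocated 1:1 and are followed for 3 years. Two-sided alpha is 0.05 and loss to follow-up 20%, giving 758 per group and 1,516 in total. The calculation mentions no interim look.

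**The concern.** For a time-to-event endpoint, an interim analysis is worth what its event count is worth. Half the patients is not half the information when accrual takes 2 years and the endpoint matures over 3. If accrual is uniform, the patients in hand at half enrolment have been followed for 6 months on average, and half of them have not reached their first six-monthly scan (Postoperative follow-up section).

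A DSMB that may stop for superiority or futility could therefore be handed a DFS comparison that supports neither. Stopping on it could end a 1,516-patient trial on chance. Stopping for superiority at a lenient level would also spend type I error that the final test at 0.05 does not allow for.

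**Working it through.** **Inputs** (all from Number of research cases): 3-year DFS 85% and 78%; margin 0.90; two-sided alpha 0.05; power 80% (the text prints β = 0.8, read here as power); uniform accrual over 2 years; 3 further years of follow-up; 20% loss. Assumptions added here: exponential DFS, and loss as an exponential hazard reaching 20% at 3 years.

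**Hazards per year.** −ln(0.85)/3 = 0.0542 and −ln(0.78)/3 = 0.0828, so the design hazard ratio (HR) is 0.654. Loss hazard: −ln(0.80)/3 = 0.0744.

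**Reproducing the plan's sample size.** Required events: 4(1.960 + 0.842)² / [ln(0.654) − ln(0.90)]² = 308. The probability of an observed event by year 5 is 0.169 (high ligation) and 0.245 (low ligation), mean 0.207. Then 308.3/0.2067 gives 746 per arm after rounding up, 1.6% below the stated 758. The model is close enough to use. With 758 per arm it predicts 758 × (0.1687 + 0.2448) = 313 events at 5 years.

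**Events at half enrolment.** 758 patients are in at month 12, 379 per arm, entered uniformly over the year. The probability of an observed event by then is 0.0260 and 0.0393, so 379 × 0.0260 + 379 × 0.0393 = 9.8 + 14.9 = 24.7 events.

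| Setting | Interim events | Share of final events |
|---|---|---|
| No data lag | 24.7 | 24.7/313.4 = 7.9% |
| 3-month lag | 38.2 | 12% |
| 6-month lag | 54.4 | 17% |
| No lag, no loss to follow-up | 25.4 | 25.4/360.5 = 7.0% |
| No lag, every patient followed for exactly 3 years | 24.7 | 24.7/252.4 = 9.8% |

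The lag rows let accrual continue up to the data cut.

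**What 24.7 events can show.** The standard error of the log HR is 2/√24.7 = 0.402.
- HR needed for P<0.05 against HR = 1: exp(−1.96 × 0.402) = 0.455. Against the 0.90 margin it would be 0.90 × 0.455 = 0.41.
- Expected z under the design effect: 0.4245/0.402 = 1.056. Power at 0.05: Φ(1.056 − 1.96) = 18%.
- Chance of an observed HR above 1 when the design effect is true: Φ(−1.056) = 15%.
- 95% interval around an observed 0.654: 0.30 to 1.44.

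**Type I error with two looks.** The two z statistics have correlation √0.079 = 0.28. The overall error is 1 − P(|Z1| < c, |Z2| < 1.96), where c is the interim critical value and the final test stays at 0.05.

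| Interim level | Overall type I error |
|---|---|
| 0.05 | 9.5% |
| 0.01 | 5.9% |
| 0.003 | 5.3% |
| 0.001 | 5.1% |

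**Could a proper boundary rescue this look?** Lan–DeMets O'Brien–Fleming-type spending at 8% information needs z of about 7.8, an observed HR of about 0.04. The look would then be harmless, but it could not realistically stop for efficacy.

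**When half the events arrive.** 157 events (half of 313) are expected about 2.7 years after first enrolment (2.6 without loss), after accrual has closed. At 50% information the same spending gives two-sided levels of about 0.003, then 0.049.

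**The case against.** The strongest reply is that the protocol does not commit to the procedure that does the damage. The interim is optional and is not said to test DFS. The P<0.05 sentence is a general convention, not a stopping rule. The standard set for early superiority is compelling evidence, which suggests something stricter than 0.05. Boundaries may sit in an analysis plan or DSMB charter not shown here. Lymph node yield, operative time and 30-day morbidity would be largely available at half enrolment, so a look limited to those already fits the text.

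Most of that stands, and it limits the point. Three stronger readings are not supported:

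- *The plan has a type I error of 9.5%.* That holds only if 0.05 is the interim criterion, which the document does not say. A futility stop does not inflate type I error at all.
- *An optional look adds further uncontrolled error.* The stated conditions are recruitment, implementation and data availability. None is a between-arm result, so no added error is shown.
- *The sealed randomisation list rules out a comparative interim.* The Randomly encoded files section says: "Upon study database lock and sponsor approval, a randomization list is generated and provided to the project statistician". That restricts the project statistician, which fits blinded analysts, and does not bar an independent DSMB from receiving data by arm.

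What the reply does not answer is the trigger. It is written in the protocol, and no boundary held elsewhere makes about 25 events informative about DFS.

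**Conclusion.** The point holds as a badly chosen trigger, not as a missing detail. The only interim the protocol names is set by enrolment and would find about 8% of the expected DFS events (7–10% across readings of loss and follow-up with no lag; 12–17% with a 3–6 month data lag on the main reading). At 8%, a DFS decision in either direction is unreliable: 18% power at nominal 0.05, and a 15% chance that the estimate points the wrong way when the design effect is real. The consequence for type I error is conditional: about 9.5% if 0.05 is used at both looks, 5.3% or less if the interim level is 0.003 or below.

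These figures rest on exponential DFS at the design rates, uniform 2-year accrual, and the follow-up time read as 3 years after accrual closes. Slower accrual than planned would raise the event share at half enrolment.

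**What to change.** Amend Statistical analysis in one of two ways.

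1. **Preferred:** state that the half-enrolment look covers safety and short-term outcomes only, with no between-arm DFS test and no superiority or futility stop based on DFS. The final DFS test then keeps the full 0.05.
2. **If a DFS look is wanted:** trigger it by events, at about 157, under a prespecified alpha-spending boundary. Lan–DeMets O'Brien–Fleming is one suitable choice (two-sided about 0.003, then 0.049). Because accrual will have closed by about 2.7 years, such a look could bring forward the answer but would not reduce enrolment.

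In either case, align Research ethics: any other periodic DSMB efficacy review that can lead to stopping should draw on the same spending function.

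The cost is wording in the protocol and the DSMB charter. The first option costs no alpha; the second moves the final level from 0.05 to about 0.049. It must be settled before any comparative DFS data are seen.

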### Random and blinding

#### Randomization method

Randomization will be performed by using dynamic allocation with minimization. Age (<50, ≥50 years), sex (male, female), ASA score (I, II, III), tumor location (distance from the anal margin of the tumor; high: >10 cm, median: 5–10 cm, low: <5 cm), body mass index (<25.0, 25.0–29.9, ≥30.0 kg/m^2^), preoperative clinical stage (I, II, III), and neoadjuvant therapy (not performed, chemotherapy, radiotherapy, chemoradiotherapy) are assigned random numbers. Random number rule: 0001–1516.

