#### Enrollment

In this study, a competitive enrollment method has been adopted and the dynamic minimization method will be used to control the bias of the randomized patients, such as age, sex, ASA, tumor location, body mass index, preoperative clinical stage, and neoadjuvant therapy (the weights of the seven factors are the same; the optimal allocation probability is *P *= 0.8 and the variance will be used to measure the size of the imbalance between the groups), and dynamic minimization enrollment will be achieved via an interactive network response system.

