### Study endpoints

Main endpoint indicator: The 3-year DFS rate. Secondary endpoint measures include the following: lymph node yield; operative time; postoperative (30-day) morbidity (anastomotic leakage, incision site infection, postoperative abdominal hemorrhage, gastrointestinal bleeding, intra-abdominal infection, pulmonary infection, urinary system infection, chyle leakage, postoperative intestinal obstruction, cardiovascular event, cerebrovascular event, thrombotic disease, urination disorder, other) and mortality.

Adverse reaction indicators: The occurrence of postoperative complications and treatment measures will be recorded in detail. All adverse events will be recorded and those resulting in hospital admission, prolonged hospital stay, additional surgical or medical treatment, or death will be reported.

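### Allocation is minimised on seven prognostic factors, but the log-rank test named for DFS is not tied to them; run as written it is mildly conservative and gives up some power

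*Protocol article*

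**What the plan says.** On allocation, the Randomization method section states: "Randomization will be performed by using dynamic allocation with minimization". It lists seven factors with their categories. The Enrollment section under Random and blinding adds that "the weights of the seven factors are the same", that imbalance is measured by the variance, and that the preferred arm is assigned with probability 0.8. Centre is not among the factors.

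On the endpoint, the Study endpoints section has "Main endpoint indicator: The 3-year DFS rate". The Statistical analysis section names Kaplan–Meier curves for DFS, and then "the log-rank test is used for variability, and a Cox regression model is used for regression analysis". It does not say which of the two is primary, gives neither strata nor covariates, and does not refer back to the minimisation factors.

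On the sample size, the Number of research cases section reads "Assuming 3-year DFS rates of 85% (high ligation) and 78% (low ligation), a superiority margin (hazard ratio) of 0.90", with two-sided α of 0.05, 1:1 allocation, 2 years of enrolment, 3 years of follow-up and 20% loss, giving 758 per group.

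The Data entry section mentions a statistical plan, which is not shown.

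**The concern.** Minimisation keeps the arms closer on stage, neoadjuvant therapy and the other factors than simple randomisation would. A log-rank test without strata computes its variance as if the arms could still differ on those factors by chance. When the factors predict DFS, that variance is too large: the test rejects less often than 5% under the null and loses power under the alternative. It also forgoes the precision that conditioning on strong prognostic factors brings.

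At stake is efficiency. The sample size leaves no reserve: it gives 80% power against the 0.90 margin and no more. A log-rank test against a hazard ratio of 1 cannot by itself show superiority beyond 0.90. If that margin is to decide the trial, the Cox estimate and its interval must carry the decision, so what enters that model matters.

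**Working it through.** **1. Reproducing the planned size.** Inputs are from the Number of research cases section; the printed β = 0.8 is read as 80% power.

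- Exponential hazards: control −ln(0.78)/3 = 0.0828 per year; high ligation −ln(0.85)/3 = 0.0542 per year.
- Hazard ratio: ln(0.85)/ln(0.78) = 0.654. Relative to the margin: r = 0.654/0.90 = 0.727.
- Events (Freedman): (1.960 + 0.842)² × [(1 + r)/(1 − r)]² = 7.849 × 39.94 ≈ 314. Schoenfeld: 4 × 7.849/(ln r)² ≈ 309.
- Event probability with hazard λ, loss hazard δ = −ln(0.80)/3 = 0.0744, uniform entry over 2 years and 3 further years of follow-up: λ/(λ+δ) × {1 − [e^(−3(λ+δ)) − e^(−5(λ+δ))]/[2(λ+δ)]}. This gives 0.169 (high ligation) and 0.245 (control), mean 0.207.
- Per group: 313.5/(2 × 0.2067) = 758 by Freedman, an exact match; 746 by Schoenfeld.

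The planned number is therefore reproduced by a log-rank design without strata.

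**2. Type I error under the stated minimisation.** The scheme was simulated as described: seven factors, equal weights, variance measure, probability 0.8, N = 1,516. The documents do not give the prognostic strength of the factors or the frequency of their levels. Both are assumptions, summarised by the standard deviation (SD) of the patients' log-hazard score. There were 4,903 runs per setting, analysed by an unadjusted log-rank test at nominal 0.05.

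| Assumed strength | SD of log-hazard score | Rejection rate under the null |
|---|---|---|
| none | 0 | 0.051 |
| moderate | 0.54 | 0.039 |
| strong | 0.86 | 0.037 |

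The simulation standard error is about √(0.039 × 0.961/4,903) = 0.003, so the last two rows lie clearly below 0.05. The first row shows that the conservatism comes from the prognostic factors and not from the allocation algorithm itself. A separate simulation of the same scheme, again with assumed strengths, gave about 0.040 for the plain log-rank and 0.053 for a log-rank stratified by stage and neoadjuvant therapy.

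**3. Power at the design effect.** The true hazard ratio within factor levels was set to 0.654, with about 305 to 316 events. The unadjusted analysis was compared with a Cox model containing the seven factors.

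| Strength (runs) | Null hypothesis | Unadjusted | Adjusted | Difference |
|---|---|---|---|---|
| moderate (1,000) | HR = 1 | 95.8% | 96.3% | 0.5 points |
| strong (1,500) | HR = 1 | 93.8% | 95.3% | 1.5 points |
| moderate (1,000) | HR = 0.90 | 77.6% | 81.3% | 3.7 points |
| strong (1,500) | HR = 0.90 | 71.0% | 79.3% | 8.3 points |

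The mean estimated hazard ratio was 0.664 (moderate) and 0.675 (strong) unadjusted, and 0.654 adjusted in both. Part of the loss against 0.90 arises because the unadjusted model estimates a population-average ratio, which lies nearer to the margin. The gap between methods is therefore more informative than the absolute power.

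**4. Centre.** With 20 centres, a between-centre SD of 0.4 on the log hazard (both assumed) and allocation not balanced on centre, the log-rank test that ignores centre rejected in 0.054 of null trials. It shows no conservatism.

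**The case against.** The strongest reply is that calling the test unadjusted reads something into silence. The section does not use that word, lists no Cox covariates, and stands in a condensed article that points to a statistical plan not shown. Strata and covariates are often left to such a plan. This stands as far as it goes: the absence of a covariate list is not an error. But the section is not silent on the test. It names one, without connecting it to the allocation it has described in detail, and the sample size matches a log-rank design without strata.

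It is also fair that the effect is small, rests on assumed strengths, and errs on the safe side. Against a hazard ratio of 1 the loss is hardly noticeable.

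Three stronger readings are tempting, and the documents do not support them:

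- **Ignoring centre makes the test conservative.** Centre was not used in allocation, so omitting it cannot have that effect, as step 4 shows. That "In this study, a competitive enrollment method has been adopted" may justify looking at differences between centres, but that is a separate matter.
- **The reported hazard ratio will be pulled toward 1.** It would come from the Cox model, whose covariates are not stated and may include these factors. Even without them, the shift reflects the difference between a marginal and a conditional hazard ratio (non-collapsibility), not bias in a marginal estimate.
- **Centre should be added to the minimisation now.** That changes the algorithm during the trial and could make the next assignment easier to guess at sites whose surgeons are unblinded. The protocol chose the 0.8 probability to limit that risk.

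**Conclusion.** The point holds as an efficiency improvement, not as a threat to validity. Run as written, the log-rank test has a size of about 0.04 instead of 0.05. It loses about 0.5 to 1.5 points of power against a hazard ratio of 1, and about 4 to 8 points against 0.90. The direction is secure whenever the minimisation factors predict DFS. The sizes depend on assumed strengths (SD of the log-hazard score 0.54 to 0.86) and level frequencies, on exponential DFS, and on taking 0.654 as the hazard ratio within factor levels. The larger loss applies only if the 0.90 margin is what the trial must beat.

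**What to change.** State one primary DFS analysis that accounts for the minimisation factors and takes test and hazard ratio from the same model. There are two workable forms:

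- a Cox model with treatment and the seven factors, in the categories used for minimisation; or
- a log-rank test and a Cox model, both stratified by clinical stage and neoadjuvant therapy.

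The first uses all seven factors. Their categories need 1 + 1 + 2 + 2 + 2 + 2 + 3 = 13 parameters, 14 with treatment, so about 314 events give roughly 22 per parameter. The second has 3 × 4 = 12 strata, some of them probably sparse because the protocol advises against neoadjuvant therapy in stage I; a pooling rule should be fixed beforehand. In either form, say whether the confidence interval is judged against 1 or 0.90. Keep the unadjusted log-rank as a sensitivity analysis.

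The cost is a change of wording, made before any comparison by arm is seen. All seven factors are recorded at allocation, and neither the sample size nor the allocation system has to change.
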